#### Duration

In **year 1**, the IOTA phase 3 study protocol will be implemented in the different participating centres. Data collection with minor built-in quality checks will occur similarly as in IOTA phase 2. At the end of year 1, complete data of 1,000 patients will be available.

In **year 2**, data collection will continue until the target sample size of 2,000 patients is reached. At the end of data registration, a detailed data quality control will be applied. All mathematical models developed in IOTA phase 1 and 2 will be prospectively validated as 1st stage test. At the end of year 2, the predictive performance of two 2nd stage tests in case of difficult tumours will also be validated: 3D power Doppler and a logistic regression model using grey scale ultrasound that was specifically constructed for difficult tumours.

In **year 3**, the validation of the three remaining 2nd stage tests will be investigated: intravenous ultrasound contrast agents, proteomic analysis and new tumour markers. During the third year different publications each highlighting different second stage tests will be prepared as well as overall study reports in high impact medical journals (e.g. JCO, J Natl Cancer Inst...)

No problems are expected with the data collection, data quality control and data storage, and data analysis since these will be similar to the successful IOTA phase 2 study and because of the existing expertise in the IOTA group.

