### 10. Statistical analysis

New mathematical models have been constructed in IOTA phase 1 and 2. In phase 3 these models will prospectively be evaluated in terms of sensitivity and specificity and overall accuracy (i.e. the proportion of the sum of true positives and true negatives over the total number of cases). Independent risk factors for malignancy will be expressed as odds. The models will be compared by constructing receiver operating characteristic (ROC) curves.

In addition new models based on new variables will be constructed. The data will be thoroughly inspected using univariate analyses (contingency tables and basic descriptive statistics) and multivariate analyses (principal component analysis, biplots, scattermatrices, canonical correlation analysis and logistic regression) to explore the data and to detect multicollinearity and outliers. Manual checks of any outliers will be performed to eliminate mistakes that had occurred during submission of the data.

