#### **Work package 4:**

##### ***Objective 4: Validation of new set of tumour markers***

External validation is needed to test the added value of combinations of novel tumour markers to the standard clinical and ultrasound variables in patients with adnexal tumours. Therefore, two tasks have to be executed:

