#### **Task 4.1: Data collection**

In tumours needing a 2nd stage test in order to make a reliable preoperative diagnosis, a blood sample is taken and later on a combination of the following markers will be assessed:

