6. HE4
7. Mesothelin
8. Osteopontin
9. kallikrein(s)

However, if in the meantime more promising markers are proposed, some of these markers may be replaced by others.

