## Task 4.2: Validation of the model

Similarly as to the validation of 2nd stage tests in WP2, each new tumour marker will be assessed using a case-control study design with tumours where a new marker was present considered as “cases” and difficult masses present in the data of IOTA 1, 1b and 2 that match the “cases” in type of tumour and patient’s age (<50 versus ≥50) considered as “controls”. Each new tumour marker will be validated in terms of possible increased sensitivity or specificity.

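### Work package 4 asks about marker combinations, but Task 4.2 judges each marker alone, on a gain in either sensitivity or specificity, from a list that is never locked

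*Protocol*

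**What the plan says.** **Aim.** Under Objective 4 of WP4: "External validation is needed to test the added value of combinations of novel tumour markers to the standard clinical and ultrasound variables". The consortium's state-of-the-art text on O4 gives the reason. A single CA-125 measurement had added nothing to expert ultrasound or to the logistic regression models, so combinations have to be tested. Task 4.1 uses the same language: "later on a combination of the following markers will be assessed".

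**Analysis.** Task 4.2 works marker by marker: "each new tumour marker will be assessed using a case-control study design". The controls are difficult masses from the earlier IOTA phases, matched on tumour type and age group. The criterion is: "Each new tumour marker will be validated in terms of possible increased sensitivity or specificity".

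**Marker list.** Task 4.1 has nine numbered entries. The first, CA 125 II, is an established marker, and the ninth, kallikreins, may stand for more than one assay. The list stays open: "However, if in the meantime more promising markers are proposed, some of these markers may be replaced by others". No closing date is given.

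**Timing.** The Duration section ends data collection in year 2 and places three second stage evaluations in year 3: "intravenous ultrasound contrast agents, proteomic analysis and new tumour markers".

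**Comparison within the Protocol.** Task 6.2 sets a two-sided condition for the difficult-tumour model: a 10% increase in specificity, with sensitivity equivalent in the two arms. Task 4.2 has no counterpart.

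**The concern.** Three features of the text combine.

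1. **The analysis does not match the aim.** A series of single-marker comparisons cannot show whether a combination adds to routine clinical and ultrasound data. No combination is named as the one that decides WP4.
2. **Either measure suffices.** Sensitivity and specificity can be traded against each other by moving a cut-off. In the extreme, calling every mass malignant gives 100% sensitivity and 0% specificity, whatever the marker measures. A criterion that accepts a gain in one measure and is silent on the other does not separate a useful marker from a shifted threshold.
3. **The set of markers is not fixed.** Samples are assayed later and evaluated after data collection has closed. Nothing in the text requires the list to be settled before histology can be linked to assay results.

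At stake is a statement that some marker has been validated for difficult masses when the result reflects the number of looks or the choice of cut-off. Meanwhile the question that WP4 was set up to answer would have no defined analysis.

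**Working it through.** **Nothing to reproduce.** The Protocol gives no alpha, sample size, power or error rate for WP4. Section 10 offers only general methods, for example "The models will be compared by constructing receiver operating characteristic (ROC) curves". The figures below therefore measure the consequence under stated assumptions. They do not check a stated number.

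**Inputs**
- Markers m: 8 new ones, or 9 with CA 125 II (Task 4.1 list).
- Measures per marker: 2 (Task 4.2), hence 2 × 8 = 16 or 2 × 9 = 18 tests.
- Level a per test, one-sided because only increases count: 2.5% or 5% (assumption).
- Correlation ρ between markers within one measure: 0 to 0.9 (assumption). The sensitivity tests and the specificity tests are taken as independent of each other, because they use malignant and benign tumours respectively.
- All markers useless, and no bias from the historical controls (assumption).

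**Independent tests.** P(at least one false success) = 1 − (1 − a)^(2m).
- 16 tests: 1 − 0.975^16 = 33.3%; 1 − 0.95^16 = 56.0%.
- 18 tests: 1 − 0.975^18 = 36.6%; 1 − 0.95^18 = 60.3%.

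**Correlated tests.** With equicorrelated normal statistics and c the (1 − a) normal quantile, the chance of no false success within one measure is B = ∫ φ(u) Φ((c − √ρ·u)/√(1 − ρ))^m du. Over both measures the chance of at least one is 1 − B².

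At ρ = 0.5:
- m = 8, a = 2.5%: B = 0.8748, 1 − B² = 23.5%.
- m = 9, a = 2.5%: B = 0.8652, 1 − B² = 25.1%.
- m = 8, a = 5%: B = 0.7809, 1 − B² = 39.0%.
- m = 9, a = 5%: B = 0.7666, 1 − B² = 41.2%.

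Across the range of ρ:

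| ρ | m = 8, 2.5% | m = 9, 2.5% | m = 8, 5% | m = 9, 5% |
|---|---|---|---|---|
| 0 | 33% | 37% | 56% | 60% |
| 0.3 | 28% | 30% | 46% | 49% |
| 0.5 | 23% | 25% | 39% | 41% |
| 0.7 | 18% | 19% | 31% | 32% |
| 0.9 | 12% | 12% | 21% | 21% |

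A simulation of the m = 9 case with 400,000 replicates agrees to within 0.2 percentage points.

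**Limit of coinciding contrasts (ρ = 1).** Only two distinct tests remain: 1 − 0.975² = 4.9% and 1 − 0.95² = 9.8%.

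**Effect of adjustment.** Bonferroni over 18 tests uses 0.05/18 = 0.0028 per test. The chance of at least one false success is then 1 − (1 − 0.0028)^18 = 4.9% under independence, computed with the unrounded level.

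**The case against.** **The statistical analysis plan is not shown.** A multiplicity rule, an alpha and a hierarchy may all stand there, so their absence from the Protocol is not a fault in itself. This stands, and the point does not rest on it. It rests on what the Protocol does fix: single-marker evaluation, the either-or criterion, and an open list beside an aim about combinations.

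**Validation may mean estimation.** Task 1.4 uses the word for computing AUC, sensitivity, specificity and predictive values, and WP4 states no significance test or pass mark. This also stands. The percentages therefore describe what would follow if the criterion were applied through tests at the assumed levels. The mismatch with the aim, and the missing condition on the second measure, matter under estimation too.

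**The contrasts may nearly coincide.** Task 4.2 follows the WP2 design, in which the quantity compared is the accuracy of the investigator's diagnosis in cases against matched historical controls. If most patients have all markers measured, the case and control groups are much the same for every marker, and the error approaches the 4.9% and 9.8% limits. That reading is possible and the text does not settle it. It weakens the arithmetic, but under it the design could not tell one marker from another.

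**Replacement is not addition.** The text speaks of swapping markers when better ones are proposed, not after looking at trial results. A swap prompted by outside evidence does not enlarge the family of tests. That is fair. What remains is that nothing requires the swap to come before linkage to histology.

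**A stronger reading.** A reader might infer that a useless panel is likely to yield a falsely validated marker. The figures do not support that. The chance passes 50% only at the one-sided 5% level with tests that are independent or close to it, which is implausible for markers measured in overlapping patients.

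**Conclusion.** The point holds as a defect in how WP4 is specified. Task 4.2 does not evaluate the combinations that Objective 4, Task 4.1 and the O4 background call for. Its criterion accepts a gain in one measure at any cost to the other, and the marker list has no lock.

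The inflation is material but uncertain. Taking ρ = 0.5 as the central assumption, roughly one useless set in four gives a false success at 2.5%, and two in five at 5%. Across all correlations up to 0.9 the range is 12% to 60%, with a floor of about 5% to 10% if the contrasts coincide. These figures assume one-sided tests at levels that the Protocol does not state, eight or nine markers, equal correlation and unbiased historical controls. Bias from those controls could move them either way and is a separate matter.

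The documents do not support two further claims: that a false finding is more likely than not, or that multiplicity control is absent from the trial's plans as a whole. The change is worth making before the year-3 analysis.

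**What to change.** 1. Reconcile Task 4.2 with Objective 4 and Task 4.1. Name one prespecified marker combination, used on top of the routine clinical and ultrasound variables, as the deciding WP4 contrast.
2. State the criterion jointly: a gain in sensitivity or specificity without loss in the other, on the pattern of Task 6.2, with the tolerance for loss written down.
3. Lock the marker list, including which kallikreins are meant, before any assay result is linked to histology. Year-3 evaluation of stored samples makes this feasible.
4. Report single markers, including late replacements, as exploratory, or test them with a Holm adjustment over the locked list. With 16 or 18 tests and an overall 5% level, the first Holm step is 0.05/16 = 0.0031 or 0.05/18 = 0.0028.

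The cost is a few sentences of protocol text and little extra analysis. The downside is that single-marker results will look less favourable and late markers can only be exploratory.

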### Work package 5:

#### *Objective 5: Validation of 3D power Doppler*

The aim of this study is to evaluate the potential benefit of 3D power Doppler as a second stage examination in order to be able to classify the difficult masses more correctly as benign or malignant.

### Task 5.1: Data collection

In centres where a 3D ultrasound equipment is available, 3D power Doppler volumes of the adnexal mass will be collected. The vascularisation index will be calculated and the vascular tree described. This will be performed in the centre where the volumes are collected. Afterwards a copy of all of the stored 3D volumes will be sent to [name] (University Hospital, Malmö, Sweden) where she will independently recalculate all of the vascularisation indices. In this way, we will be able to correct for interobserver variability.

### Task 5.2: Validation of the model

A case-control study will be performed to validate the use of 3D ultrasound as a second stage test. Masses in IOTA Phase 3 which have been investigated with 3D ultrasound are denoted as the “cases”. A historical control group is constructed using data of difficult masses available in IOTA Phase 1, 1b and 2. Two matching factors will be applied: 1) same tumour type and 2) age (<50 versus ≥50). This will enable us to assess whether 3D ultrasound results in a higher detection rate of malignant masses (higher sensitivity) or a decrease in the number of unnecessary exploratory laparotomies (higher specificity).

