#### **State of the art in the consortium and comparative advantage**

#### **O1: Prospective external validation of predictive mathematical models and pattern recognition to distinguish between malignant and benign adnexal masses**

**IOTA phase 1.** During IOTA phase 1 we collected more than 50 ultrasound, demographic and clinical variables of 1,066 patients with an adnexal mass. A histopathologic diagnosis was available for all patients. Patients were collected in 9 different international centres where the ultrasound examination was performed by one of the IOTA expert sonologists following a standardised protocol. In this way we obtained a large and multicentre database that is more likely to resemble the general population [44].

Based on this dataset 12 mathematical models were developed (2 logistic regression models [44], 1 scoring system (unpublished data), 3 neural networks [46] and 6 kernel based models [47] (3 support vector machine models (SVM) and 3 relevance vector machine models (RVM)). On the test set of IOTA phase 1 all models obtained an area under the ROC curve (AUC) of more than 0.92.

**IOTA phase 1b.** In IOTA phase 1b a new dataset of 507 new patients was prospectively collected in 3 of the 9 IOTA centres. All models proved to perform excellent with again AUCs of more than 0.94 (unpublished data).

**IOTA phase 2.** The aim of IOTA phase 2 was to test the IOTA models in new centres with different population characteristics and different levels of ultrasound experience. More than 2,000 patients have been included in 20 centres throughout the world. In a preliminary analysis the main logistic regression model (1) was tested and in every centre the AUC was above 0.87. When tested on the whole dataset the AUC was above 0.93. In IOTA phase 1 and 2 we found that both for the expert sonologist using pattern recognition (subjective impression) as for the mathematical models, approximately 8% of the adnexal masses were difficult to classify as benign or malignant and lied close to the decision boundary. Models that were built especially for the classification of these difficult masses showed disappointing results [45].

**IOTA phase 3 .** During IOTA phase 3, the same centres that participated in IOTA phase 2 will prospectively include a new dataset of more than 2,000 patients but will now be able to evaluate the prediction of the main logistic regression model immediately after performing the ultrasound scan.

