### **Task 2.2: Validation of the model**

The presence, the amount of vascularisation (colour score) and the pattern (regular or chaotic) of blood flow detected with colour Doppler and contrast-enhanced images will be investigated to assess whether the use of CnTI technology provides advantages with respect to the unenhanced ultrasound examination in the assessment of gynaecologic diseases, as seen in the preliminary results. Results will be validated using a case-control design. The above tumours for which intravenous contrast agents have been applied are considered as the “cases”. In IOTA 1, 1b and 2 a “historical control group” of difficult masses will be composed with two matching factors: 1) the same tumour type and 2) age (<50 versus ≥50). The difference in sensitivity and specificity of the investigator’s diagnosis between the cases with intravenous contrast and the control group will be assessed. The value of quantitative assessment of contrast ultrasound as second stage test in difficult tumours will also be compared with other second stage tests that were applied in the same patients.

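### Tasks 2.2, 4.2 and 5.2 validate second-stage tests mainly against historical controls, so a gain cannot be attributed to the test; Task 4.2 also leaves the scored classification undefined

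*Protocol*

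**What the plan says.** Three of the five second-stage validations share one design. Task 5.2 (3D power Doppler) states: "A historical control group is constructed using data of difficult masses available in IOTA Phase 1, 1b and 2". It goes on: "Two matching factors will be applied: 1) same tumour type and 2) age (<50 versus ≥50"). Task 2.2 (contrast) uses the same controls and matching factors and names its measure: "The difference in sensitivity and specificity of the investigator’s diagnosis between the cases with intravenous contrast and the control group will be assessed". Task 4.2 (markers) says it works in the same way as work package 2 and concludes: "Each new tumour marker will be validated in terms of possible increased sensitivity or specificity".

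Other sections describe what is new in Phase 3:
- **LR1 disclosure.** The consortium section on O1 says that participating centres "will now be able to evaluate the prediction of the main logistic regression model immediately after performing the ultrasound scan".
- **Difficult-tumour model.** The consortium section on O6 says investigators will have this model's prediction. Task 6.1 randomises access to it 1:2.
- **Choice of test.** The same O6 section leaves the choice among contrast, proteomics, markers and 3D Doppler to the investigator's preference.
- **Trigger.** Task 1.5 requires a second-stage test for the 15% of masses nearest the LR1 decision boundary, about 300 patients.
- **Order of recording.** Task 1.2 freezes the subjective assessment before any model output is shown.

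For the markers, Task 4.1 says that "a blood sample is taken and later on a combination of the following markers will be assessed", and the Duration section puts their validation in year 3, after data collection has ended.

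**The concern.** A historical comparison isolates the test only if the test is the main thing that changed between the periods. Here several things changed together, and matching on tumour type and a two-level age split does not address them. A test with no diagnostic value could be reported as raising sensitivity or specificity in difficult masses, and a useful one could be masked. These results are meant to feed the optimal diagnostic algorithm for women in whom malignancy cannot otherwise be ruled out.

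Work package 4 has a further gap. If it scores the investigator's diagnosis, as the link to work package 2 suggests, a marker measured after that diagnosis cannot have influenced it.

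**Working it through.** **1. The plan's own figure.** Task 1.5: 0.15 × 2,000 = 300 difficult masses. This reproduces. No sample size, power or significance level is stated for work packages 2, 4 or 5.

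**2. What differs between cases and controls.**

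| Feature | Phase 3 cases | IOTA 1, 1b, 2 controls | Matched? |
|---|---|---|---|
| Tumour type, age split at 50 | – | – | yes |
| Examiner saw LR1 | yes | no (inferred from the wording on O1) | no |
| Difficult-tumour model shown | possibly | no (developed from these data) | no |
| Choice of second-stage test | investigator preference | not applicable | no |
| Period | Phase 3 | earlier phases | no |
| Route to being difficult | LR1 15% band or uncertain assessment | mainly examiner uncertainty | no |

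**3. Share of masses called difficult.** From the consortium section on O6: 90/1,066 = 8.4% (IOTA 1), 39/507 = 7.7% (IOTA 1b), 250/3,500 = 7.1% (all phases). At 7.1% to 8%, 2,000 patients would give 143 to 160 difficult masses. The LR1 rule gives 300, about twice as many.

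**4. Illustration: mix alone, no test effect.** Let u be the examiner-uncertain share (0.071 or 0.08), s1 the specificity in those masses (assumed 0.5 to 0.7) and s2 the specificity in the remaining near-boundary masses (assumed 0.8 to 0.95). Assume that the uncertain masses lie within the 15%, that controls are chosen by examiner uncertainty, and that matching does not remove the difference in difficulty.

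Phase 3 specificity = [u·s1 + (0.15 − u)·s2] / 0.15; spurious gain = that value − s1.
- Smallest: (0.08 × 0.7 + 0.07 × 0.8)/0.15 = 0.747; gain 0.047.
- Largest: (0.0714 × 0.5 + 0.0786 × 0.95)/0.15 = 0.736; gain 0.236.

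The range is about 5 to 24 points. Task 6.2 regards 10 points as clinically relevant.

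**5. Illustration: LR1 disclosure alone, no test effect.** Suppose that seeing LR1 adds d to specificity and the test adds nothing. With n benign masses per group and a two-sided 5% test (both assumed), the chance of declaring a gain is Φ[(d − 1.96·SE0)/SE1]. Here p̄ is the mean of the two specificities p1 and p2, SE0 = √(2p̄(1 − p̄)/n), and SE1 = √[(p1(1 − p1) + p2(1 − p2))/n].
- Example: n = 150, 0.80 v 0.90. SE0 = 0.0412, SE1 = 0.0408, so Φ[(0.10 − 0.0808)/0.0408] = 0.68.
- Over n = 50 to 150 and control specificity 0.5 to 0.8: 17% to 68% for d = 10 points, and 7% to 21% for d = 5 points.

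**6. Precision of a paired alternative.** Assume 150 benign masses and specificity 60% v 70%. The unpaired 95% half-width is 1.96·√[(0.24 + 0.21)/150] = 10.7 points. The paired half-width is 1.96·√[(D − 0.01)/150] for discordance D: 4.8, 7.0, 8.6 and 10.0 points at D = 10%, 20%, 30% and 40%. Pairing gains precision unless discordance is high, but its main benefit is that it removes the confounding.

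**7. Work package 4 timing.** Under Task 4.1 and the Duration section, markers are assayed later and validated in year 3. The O6 section lists them among tests that investigators can apply. The two descriptions do not agree, and Task 4.2 does not say whether an investigator diagnosis, a marker cut-off or a combined model is scored.

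**The case against.** The strongest reply is that the plan is better than the historical comparison alone suggests, and that details may sit in a statistical analysis plan. Much of the first part stands. The second does not help, because the protocol itself fixes the comparator and the matching.

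Several stronger readings are tempting but not supported:
- **That controls had no LR1 value.** LR1 was built on or validated in the earlier phases, so it can be computed for them. What differed is whether the examiner saw it.
- **That the definition of difficult changed outright.** Work package 1 counts uncertain assessment or uncertain prediction in Phase 3, and the O6 section allows near-boundary masses in earlier phases. Both routes exist in both periods, so the concern is the mix.
- **That Task 5.2 sets unselected masses against difficult ones.** Task 5.1 does not restrict the volumes, but the stated aim of work package 5 is to classify difficult masses.
- **That nothing in work package 2 is interpretable.** Each patient has an unenhanced and an enhanced scan, and contrast "will also be compared with other second stage tests that were applied in the same patients". Confounding by phase does not affect these comparisons.
- **That Task 4.2 cannot reflect the marker at all.** This holds only if the investigator's diagnosis is scored. Work package 4 aims at the added value of marker combinations. If a marker rule or combined model is scored, the result does contain the marker, though still confounded.
- **That higher sensitivity or higher specificity is a formal success rule.** Task 5.2 says what will be assessed; it sets no criterion.
- **That drift between phases is already shown.** Examiner specificity went from 762/800 = 95.3% to 338/364 = 92.9% (difference −2.4 points, 95% CI −5.4 to +0.6). Sensitivity went from 234/266 = 88.0% to 129/143 = 90.2% (+2.2, CI −4.0 to +8.5). Both are compatible with chance, and they cover all masses in 9 versus 3 centres.
- **That nine markers on two measures give a 60% chance of a false success.** 1 − 0.95^18 = 0.60 needs independence and 5% per favourable result. Counting only the favourable tail gives 1 − 0.975^18 = 0.37, and markers in the same women are unlikely to be independent.

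The frozen assessment does not rescue the historical comparison. It precedes LR1, and so the test that LR1 triggers; any later diagnosis carries LR1 as well as the test.

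**Conclusion.** The concern holds for the main validation in Tasks 2.2, 4.2 and 5.2. As designed, a difference in sensitivity or specificity from the historical controls cannot be attributed to the second-stage test. That examiners in earlier phases did not see LR1 is inferred from the wording on O1 rather than stated.

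The size of the bias cannot be derived from the protocol. The 5 to 24 points and the 17% to 68% show that, under plausible assumed values, the bias could exceed the 10 points that the protocol treats as relevant for work package 6. They are not estimates.

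Work package 2 is partly protected by its same-patient comparisons; work packages 4 and 5 state none. In work package 4 the scored classification is undefined, and the accounts of when markers become available conflict. Work package 1 and the randomised comparison in work package 6 are not affected.

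**What to change.** - **Primary analysis in Tasks 2.2, 4.2 and 5.2.** Replace the historical comparison with a within-patient comparison in Phase 3 difficult masses, as defined in work package 1 and Task 1.5. Compare pre-test information (frozen assessment and LR1) with and without the second-stage result in the same women.
- **Measures.** Use a paired AUC difference, with cross-validation or optimism correction for any newly fitted combined model. Add a paired comparison of specificity at non-lower sensitivity, in line with Task 6.2.
- **Task 4.2.** State that a marker rule or combined model, not the investigator's diagnosis, is scored. Adjust for multiplicity across markers, for example by Holm. Reconcile Task 4.1 and the Duration section with the O6 section on whether investigators have marker results.
- **Historical comparison.** Keep it as descriptive, with the differences in the table above acknowledged.

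**Cost.** The frozen assessment, LR1 value, test result and histology come from the same women, so the model-based comparison needs only modest extra analysis. A reader-based comparison needs two items that the protocol does not describe: the examiner's diagnosis after LR1 but before the test, and again after the test.
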